## **Protocol**

This supplement contains the following items:

1. Original protocol, which was unchanged and only one version exists.
2. Original statistical analysis plan, which was unchanged and only one version exists

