**Sample size estimation:**

A total of 278 patients will be recruited to achieve 250 per-protocol (PP) patients.

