### 3.6 Sample size

The sample size determination is based on the result of our retrospective data.[16] The estimated proportions of CAL are 17% after IVIG and high-dose aspirin combination treatment and 15.4% after IVIG alone treatment. We consider the difference less than 10% is of no clinical importance. The following contents are the statistical basis for estimating sample size for this trial.

$$H_0: P_T - P_S \leq \delta$$

$$H_A: P_T - P_S > \delta$$

$$P_T: \text{CAL-free rate in test group} = 0.846$$

$$P_S: \text{CAL-free rate in standard group} = 0.83$$

$$\delta = -0.1$$

Assume that the type I and type II error rates are  $\alpha = 0.05$ ,  $\beta = 0.2$ , respectively. The clinically meaningful difference  $\delta$  is -0.1. The CAL-free rate of test group (IVIG alone)  $P_T$  is 0.846 and that of standard group (IVIG + high dose aspirin)  $P_S$  is 0.83.

Assume the sample sizes of two groups are equal, the sample size of each group for the non-inferiority trial is 125 patients. Offsetting a maximal dropout of 10%, 139 patients are required for per group. That is, a total sample size of 278 patients is required for the trial.

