### **3.11 Statistical methods**

All baseline characteristics will be used to investigate comparability of both trial arms. The primary outcome evaluation (CAL rate at 6-8 weeks) and secondary outcome of Z score of coronary arteries and CAL rate at 6 months will be performed on per-

protocol (PP) population while the other secondary outcome will be performed on intention-to-treat (ITT) population. Continuous variables will be described by using the mean (standard deviation) or median (interquartile range) as appropriate, categorical variables by using count (percentage). The participant characteristics will be compared using a  $\chi^2$  test for categorical variables, and a t test or Wilcoxon rank sum test for continuous variables. P values < 0.05 will be considered statistically significant.

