### **Appendix B: Case Report Form**

### **Appendix C: Common Terminology Criteria for Adverse Events (CTCAE) version**

**4.03. (A complete copy of the CTCAE version 4.03 will be held in each site study file)**

## **Statistical analysis**

All of the baseline characteristics are used to study the comparability of both trial arms. The primary outcome evaluation and safety evaluation are carried out on the intention-to-treat (ITT) population. Continuous variables will be described using either the mean (standard deviation) or median (interquartile range), as appropriate, and categorical variables will use count (percentage). Participants' characteristics are compared using a  $\chi^2$  test for categorical variables and a t-test or Wilcoxon rank sum test for continuous variables.  $P$ -values < 0.05 are considered statistically significant.

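### The protocol analyses the primary endpoint per-protocol and the SAP analyses it by intention-to-treat, with no rule saying which prevails, so the primary set stays open to choice after the data are seen

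*Combined protocol and SAP*

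**What the plan says.** In protocol 3.11 a single sentence assigns the populations. It opens with "The primary outcome evaluation (CAL rate at 6-8 weeks) and secondary outcome of Z score of coronary arteries and CAL rate at 6 months" and ends, after the prefix per-, with "protocol (PP) population while the other secondary outcome will be performed on intention-to-treat (ITT) population". CAL at 6-8 weeks, coronary Z scores and 6-month CAL are therefore PP outcomes, and the remaining secondary outcomes are ITT.

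The Protocol Synopsis (Sample size estimation) sizes the trial on the same population: "A total of 278 patients will be recruited to achieve 250 per-protocol (PP) patients".

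The SAP, under Statistical analysis, reads: "The primary outcome evaluation and safety evaluation are carried out on the intention-to-treat (ITT) population". It assigns no set to Z scores or 6-month CAL.

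The opening page lists the two documents as "Original protocol, which was unchanged and only one version exists" and "Original statistical analysis plan, which was unchanged and only one version exists". Neither is marked as superseding the other.

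The available text does not say who belongs to PP or ITT, what happens when the 6-8-week echocardiogram is missing, or whether the two analyses must agree. Section 3.9 says that participants and investigators know the arm.

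**The concern.** The two sections give different answers to the same question, and the question governs the trial's only confirmatory conclusion. Because both texts are current, an analyst could cite either one in good faith.

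The choice matters more here than in a superiority trial. PP gives up the protection of randomisation, and ITT can dilute a real difference between arms. A result close to the margin can pass in one set and fail in the other.

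The sets also need not differ at random. Under Withdraw criteria in section 3.2, patients leave for allergic reactions, for adverse events that lead to stopping study treatment, and on investigator judgement. Only one arm receives high-dose aspirin, and the arm is known. With PP undefined, both its membership and the choice of set could be settled by people who know the allocation.

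**Working it through.** **Inputs.** Section 3.6 gives CAL rates of "17% after IVIG and high-dose aspirin combination treatment and 15.4% after IVIG alone treatment", that is CAL-free rates of 0.83 (standard) and 0.846 (test). It states the margin as "We consider the difference less than 10% is of no clinical importance", so δ = -0.10 on the CAL-free rate. It also gives α = 0.05, β = 0.2, equal groups and 10% dropout. It does not say whether α is one- or two-sided.

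**1. Reproduce the plan's sample size.** With unpooled variance and one-sided α = 0.05:

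n = (1.645 + 0.842)² × (0.83×0.17 + 0.846×0.154) / (0.016 + 0.10)² = 6.18 × 0.2714 / 0.01346 ≈ 124.7, so 125 per group.

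125 / 0.9 = 138.9, so 139 per group and 278 in total. All three figures match. One-sided 0.025 would give 159 per group, so the stated size rests on one-sided 0.05. That level is used below.

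**2. Can the choice of set change the verdict?** The lower bound is d - 1.645 × √[p_T(1-p_T)/n + p_S(1-p_S)/n], where d = p_T - p_S. Non-inferiority needs a bound above -10 points. The counts are invented to show the mechanism.

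| CAL-free, test vs standard | Set | Lower bound (points) | Verdict |
|---|---|---|---|
| 101/125 vs 104/125 | PP | -10.4 | fails |
| 113/139 vs 116/139 (12 of 14 extra patients CAL-free in each arm) | ITT | -9.7 | passes |
| 102/125 vs 104/125 | PP | -9.5 | passes |
| 102/139 vs 104/139 (14 missing per arm counted as CAL) | ITT | -10.1 | fails |

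First row in full: 0.808 - 0.832 - 1.645 × √[(0.1551 + 0.1398)/125] = -0.024 - 0.080 = -0.104.

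The verdict can flip in either direction.

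**3. How often?** This comes from a simulation of 400,000 trials per scenario with the same bound. PP has 125 per arm and ITT has 139 per arm. The 14 extra patients per arm have an observed outcome but lie outside PP. That number takes the plan's whole dropout allowance (139 - 125). The rates for these patients are assumptions, because the documents give none.

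| Scenario | PP succeeds | ITT succeeds | Verdicts disagree | Either succeeds | Both succeed |
|---|---|---|---|---|---|
| Design rates in everyone | 80.4% | 83.8% | 7.2% | 85.7% | 78.5% |
| Design rates, but test-arm extras 0.70 CAL-free | 80.5% | 73.1% | 10.8% | 82.2% | 71.4% |
| True difference at the margin (0.73 vs 0.83) in everyone | 5.1% | 5.0% | 2.7% | 6.4% | 3.7% |

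In the last row every success is a false claim of non-inferiority. Either set named in advance holds the error at about 5%. A free choice of the favourable set raises it to 6.4%.

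**The case against.** The strongest reply is that the intent is clear: 3.11 and the Synopsis both point to PP. That is a fair reading of the protocol, but the SAP says the opposite about the same outcome and no text ranks the two documents.

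A second reply is that the sets may hardly differ. The 10% in 3.6 is described as a maximal dropout. Patients lost to follow-up or withdrawing consent may have no 6-8-week echocardiogram, and so no observed outcome in either set. Without imputation PP and ITT could then nearly coincide. This stands: the figures above would shrink, and the result would depend on a missing-data rule that the available text does not give.

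Some stronger readings are tempting, but the documents do not support them:

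- A reader might infer that the error rate is out of control. Under equal rates the inflation is from about 5% to about 6.4%. Larger figures need assumed rates in the excluded patients. For example, with PP at the margin and extras at 0.78 in both arms, either set succeeds in 8.1% of trials. But the true ITT difference there is 125/139 × -10 = -9.0 points, inside the margin, so an ITT success is not a false claim about the ITT difference.
- A reader might infer that the set was chosen after the results. The documents leave that possible and do not show that it happened.
- A reader might treat the absence of a requirement that both sets succeed as an error in itself. It is not, because one named primary set with the other as support is also a sound plan.

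**Conclusion.** The plan is wrong as written. Two current documents assign the primary endpoint to different analysis sets and nothing in the available text settles which applies. Pages that are not available could hold set definitions, but these two statements conflict whatever those pages say.

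The consequence is moderate. If 14 of 139 patients per arm have an outcome but lie outside PP, the verdicts disagree in about 7% of trials at the design rates, and in about 11% if the test-arm extras are 70% CAL-free. Type I error at the margin is about 6.4% instead of about 5% if the favourable set may be picked. These figures rest on one-sided α = 0.05, a Wald bound and assumed rates outside PP. They illustrate the problem and do not predict this trial's result. The direction could favour either arm.

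The correction is needed because it concerns the one confirmatory analysis and is cheap, not because the numerical effect is large.

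**What to change.** Put one identical statement in protocol 3.11 and the SAP, before any comparison by arm. It should:

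- name the primary analysis set for CAL at 6-8 weeks;
- define PP and ITT membership, with the violations that remove a patient from PP listed in advance;
- state how a missing 6-8-week echocardiogram is handled in each set;
- report the other set as a pre-specified supporting analysis.

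The alternative is to claim non-inferiority only if the one-sided 95% lower bound excludes -10 points in both sets. That level is the one that reproduces 125 per group and should be written down. Power should then be restated as about 78.5% instead of 80%, for 14 observed extras per arm at the design rates. It falls to about 71% if the test-arm extras are 70% CAL-free.

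State the analysis set for 6-month CAL consistently in both documents. Do not add a non-inferiority test to it: the objectives only compare it between arms, and it has no margin of its own.

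The main cost is wording, and naming one primary set leaves the sample size unchanged. There is one practical cost. An ITT analysis with observed outcomes needs the 6-8-week echocardiogram from patients who have been withdrawn, and the withdrawal section makes no provision for collecting it. That section must be reconciled with whichever set is chosen.

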#### Secondary outcomes

- **IVIG resistance rate:**

IVIG resistance is defined as persistent or recrudescent fever at least 48 hours but not longer than 7 days after completion of the first IVIG treatment.

- **Duration of fever after IVIG treatment**

We will record the body temperature every 6 hour during the hospitalization period.

- **Duration of hospitalization**

We will record the hospitalization duration from admission (or arriving emergency room) to discharge date.

- **Laboratory data**

Laboratory data of CBC/DC, GOT/GPT, and CRP will be checked at baseline, day 5, and 6-8 week.

- **Z score of coronary arteries**

We will estimate Z score of the proximal segments of LMCA, LAD, and RCA at baseline, Day 5, 6-8 weeks, and 6 month with 2D echocardiography. The calculation of Z score is based on the website of Taiwan Society of Pediatric Cardiology ([http://www.tspc.org.tw/service/z\\_score.asp](http://www.tspc.org.tw/service/z_score.asp)).

- **CAL rate at 6 months**

- **Adverse event (AE) and serious adverse event (SAE)**

We will record AE and SAE. Severity of AE will be based on Common Terminology Criteria for Adverse Events (CTCAE) version 4.03.

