### 3.5 Participant timeline

| Study period       | Enrolment | Randomization | Intervention | Day 5   | 6-8 weeks | 6 months   |
|--------------------|-----------|---------------|--------------|---------|-----------|------------|
| Time point         | Day -3~0  |               | Day 1        | Day 5±2 | Day 49±10 | Day 180±30 |
| Eligibility screen | •         |               |              |         |           |            |
| Informed consent   | •         |               |              |         |           |            |
| Demographics       | •         |               |              |         |           |            |
| Randomization      |           | •             |              |         |           |            |
| Intervention       |           |               | •            |         |           |            |
| echocardiography   |           |               |              | •       | •         | •          |
| Body temperature   | •         |               |              | •       | •         |            |
| CBC/DC             | •         |               |              | •       | •         |            |
| GOT/GPT            | •         |               |              | •       | •         |            |
| CRP                | •         |               |              | •       | •         |            |
| AE、SAE             |           |               | •            | •       | •         |            |
|                    |           |               |              |         |           |            |

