**Demographic Data**

**Gender:** ☐ Male ☐ Female, **Birthday:** □□□□/□□/□□ (yyyy/mm/dd)

**Body weight:** □□.□ Kg, **Body height:** □□□.□ cm, **Body temperature:** □□.□ °C

**Baseline laboratory data date:** 20□□/□□/□□ (yyyy/mm/dd)

| Item | Value | Unit       | Item       | Value | Unit    | Item       | Value | Unit |
|------|-------|------------|------------|-------|---------|------------|-------|------|
| WBC  |       | 1000/ul    | MCHC       |       | gHb/dl  | Monocyte   |       | %    |
| RBC  |       | Million/ul | RDW-SD     |       | %       | Eosinophil |       | %    |
| HGB  |       | g/dl       | RDW-CV     |       | %       | Basophil   |       | %    |
| HCT  |       | %          | PLT        |       | 1000/ul | AST/GOT    |       | U/L  |
| MCV  |       | fL         | Segment    |       | %       | ALT/GPT    |       | U/L  |
| MCH  |       | pg/cell    | Lymphocyte |       | %       | CRP        |       | mg/L |

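### Baseline laboratory values are to be collected, but the plan names no baseline-adjusted analysis of the Day 5 and 6-8 week laboratory outcomes

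*Combined protocol and SAP*

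**What the plan says.** **Methods.** Protocol section 3.11 gives "a t test or Wilcoxon rank sum test for continuous variables". The SAP (Statistical analysis) gives "a t-test or Wilcoxon rank sum test for continuous variables". In the protocol the sentence opens "The participant characteristics will be compared using a", and the SAP sentence has the same subject. Neither document names a test, model, covariate, effect estimate or confidence interval specifically for the laboratory outcomes. Both set a P value threshold of 0.05.

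**Use of baseline data.** Section 3.11 states: "All baseline characteristics will be used to investigate comparability of both trial arms". No other use is described.

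**Laboratory data.** Section 3.4 states: "Laboratory data of CBC/DC, GOT/GPT, and CRP will be checked at baseline, day 5, and 6-8 week". The timeline in section 3.5 marks CBC/DC, GOT/GPT and CRP at enrolment, Day 5 and 6-8 weeks. The Visit 1 CRF page (Day -3 to 0) has a field headed "Baseline laboratory data date" and a table of 18 items. Section 3.11 assigns these outcomes to the ITT population.

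**Coronary Z scores.** Section 3.4 states: "We will estimate Z score of the proximal segments of LMCA, LAD, and RCA at baseline, Day 5, 6-8 weeks, and 6 month". In the section 3.5 timeline, the row "echocardiography" is marked only at Day 5, 6-8 weeks and 6 months. The first echocardiography field in the CRF is on the Day 5 visit page.

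**The concern.** Laboratory data are a named secondary objective, and they bear on the reason for the trial. Section 2.1 cites hepatic toxicity and gastrointestinal bleeding among the risks of aspirin, and the title of reference 16 links high-dose aspirin with anemia. GOT/GPT and haemoglobin are the trial's laboratory measures of those risks; CRP measures residual inflammation.

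If follow-up values are compared without the baseline value, part of the between-child variation that the baseline could explain stays in the error term. Any chance difference between the arms at baseline also stays in the estimate. Section 3.8 describes permuted blocks and no stratification. The plan checks comparability but does not say what follows if the arms differ. The cost is a less sharp answer on the laboratory outcomes, when the information to sharpen it is already on the CRF.

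**Working it through.** **1. The plan's own figure.** The documents size only the primary endpoint. With CAL-free rates 0.846 and 0.83, δ = -0.1, one-sided α = 0.05 and power 0.80:

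n = (1.645 + 0.842)² × (0.846 × 0.154 + 0.83 × 0.17) / (0.016 + 0.1)² = 124.7, so 125 per arm.

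125 / 0.9 = 138.9, so 139 per arm and 278 in total. Section 3.6 is reproduced, and nothing below changes it.

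**2. Is the covariate there?**

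| Outcome | Baseline in 3.4 | Baseline in 3.5 timeline | Baseline field in CRF |
|---|---|---|---|
| CBC/DC, GOT/GPT, CRP | Yes | Yes (enrolment) | Yes (Visit 1) |
| LMCA, LAD, RCA Z scores | Yes | No | No (first field at Day 5 visit) |

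For laboratory values the three sources agree, and Visit 1 precedes randomization. For Z scores they do not. The Day 5 visit (Day 3 to 7) follows the Day 1 intervention, so its echocardiogram cannot serve as a baseline covariate.

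**3. Unadjusted detectable difference.** I assume a two-sided 0.05 test, 80% power and all 139 children per arm contributing a value:

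(1.960 + 0.842) × √(2/139) = 0.336 SD of the follow-up value.

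**4. With baseline adjustment.** For a linear model with arm and baseline, compared with an unadjusted difference on the same scale, the variance factor is 1 - r². The standard error and the detectable difference are multiplied by √(1 - r²). The documents give no r, so it is an assumption shown as a range.

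| Assumed r | 1 - r² | SE reduction | Detectable difference, 139 per arm | Power at 0.336 SD |
|---|---|---|---|---|
| 0 | 1.00 | 0% | 0.336 SD | 80.0% |
| 0.1 | 0.99 | 0.5% | 0.334 SD | 80.4% |
| 0.3 | 0.91 | 4.6% | 0.321 SD | 83.6% |
| 0.5 | 0.75 | 13.4% | 0.291 SD | 89.9% |
| 0.7 | 0.51 | 28.6% | 0.240 SD | 97.5% |

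If only 125 per arm contribute, the detectable difference is 0.354 SD unadjusted, and 0.338, 0.307 and 0.253 SD at r = 0.3, 0.5 and 0.7.

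**5. Chance imbalance.** The baseline difference between arms has standard error √(2/139) = 0.12 SD, so imbalances up to 1.96 × 0.12 = 0.24 SD are ordinary. An unadjusted estimate carries r times the imbalance: at r = 0.5 and 0.24 SD, this is 0.12 SD.

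**6. Price of the covariate.** One extra covariate in about 278 children inflates the variance by roughly 0.4%. Break-even is where r² = 0.004, that is r of about 0.06.

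**The case against.** The strongest reply is that this is a matter of efficiency, not an error. In a 1:1 randomized trial an unadjusted t or rank test is valid, and its error rate already allows for chance imbalance. That stands. A reader might infer from the imbalance argument that the unadjusted comparison is biased; it is not.

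A second reply is that the quoted sentence concerns participant characteristics. That also stands. A reader might infer that the plan commits the laboratory outcomes to unadjusted tests, but the documents do not say so. The inference rests only on no other test being named. If it is wrong, the outcomes have no stated method, and the same addition is needed.

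Third, the size of the gain is unknown. Nothing in the documents shows that follow-up values depend strongly on the starting level. Baseline is taken during acute fever and one outcome is at Day 49±10, so a low correlation cannot be excluded, and r may differ between Day 5 and 6-8 weeks. The factor 1 - r² also applies against a t test on the same scale; the gain over the Wilcoxon test, which section 3.11 also allows, has not been computed.

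Fourth, the work is more than trivial: 18 CRF items at two time points make 36 models, with choices of scale and a rule for missing baselines. This is fair, but the burden is analytic only.

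**Conclusion.** The point holds for the laboratory outcomes as an improvement at negligible cost. Baseline values are planned consistently, their only stated use is to check comparability, and no adjusted analysis is specified. Depending on an assumed r of 0.1 to 0.7, the gain runs from almost nothing (standard error 0.5% lower) to substantial (28.6% lower). I would not quote the upper end as the expected benefit. The detectable differences assume two-sided testing at 0.05 and, in the main table, complete data in 139 per arm.

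A reader might extend the point to Z scores because section 3.4 lists a baseline measurement. The documents do not support that as a free change: the timeline and CRF have no place for a baseline echocardiogram. The primary endpoint, margin and sample size are not affected.

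**What to change.** In section 3.11 and the SAP, state that each laboratory value at Day 5 and at 6-8 weeks will be analysed with a linear model containing arm and the child's own baseline value. Use the log scale for skewed values such as CRP, GOT and GPT. Report the adjusted difference, or the ratio for logged values, with a 95% CI.

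In the same text, give the rule for a missing baseline, the handling of values at or below an assay limit before logging, and the scale for the percentage differentials. It would help to say which few laboratory values are of main interest, so that 36 models are not read as equals.

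For coronary Z scores, first reconcile section 3.4, the section 3.5 timeline and the CRF on whether a baseline echocardiogram is done. If it is, use the same model at Day 5, 6-8 weeks and 6 months.

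The cost for the laboratory outcomes is a short addition to the text, one covariate per model and slightly more analysis work. No new data, visits or patients are needed.

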### **3.12 Adverse Events (AE) and Serious Adverse Events (SAE)**

#### **● Adverse Events**

An AE is any untoward medical occurrence in a subject during the participation of a clinical trial, regardless the possibility of a causal relationship. An AE can be any unfavorable signs or symptoms or diagnosed new diseases or deterioration of existing chronic or intermittent diseases. AEs will be collected after the participant has provided consent and enrolled in this clinical trial. If a subject experiences an AE after the informed consent document is signed but the subject has not started to receive treatment, the event will be reported as not related to the clinical trial.

